## Abstract

**Introduction:**

Only 30–40% of depressed patients treated with medication achieve full remission. Studies that change medication or augment it by psychotherapy achieve only limited benefits, in part because current treatments are not designed for chronic and complex patients. Previous trials have excluded high-risk patients and those with comorbid personality disorder. Radically Open Dialectical Behaviour Therapy (RO-DBT) is a novel, transdiagnostic treatment for disorders of emotional over-control. The REFRAMED trial aims to evaluate the effectiveness and cost-effectiveness of RO-DBT for patients with treatment-resistant depression.

**Methods and analysis:**

REFRAMED is a multicentre randomised controlled trial, comparing 7 months of individual and group RO-DBT treatment with treatment as usual (TAU). Our primary outcome measure is depressive symptoms 12 months after randomisation. We shall estimate the cost-effectiveness of RO-DBT by cost per quality-adjusted life year. Causal analyses will explore the mechanisms by which RO-DBT is effective.

**Ethics and dissemination:**

The National Research Ethics Service (NRES) Committee South Central – Southampton A first granted ethical approval on 20 June 2011, reference number 11/SC/0146.

**Trial registration number:**

ISRCTN85784627.

Strengths and limitations of this studyThis study tests a novel and promising psychotherapeutic intervention, specifically designed for patients with chronic depression that is hard to treat.Radically Open Dialectical Behaviour Therapy (RO-DBT) is manualised, and is increasingly used for over-controlled patients.Our inclusive sample will add general findings to the limited evidence base on interventions for refractory depression.Our mechanistic analyses will estimate the role of mediators, including therapeutic alliance and adherence to treatment, by reducing bias inherent in conventional analyses of mediation.Our comparator for the effectiveness of RO-DBT is usual clinical practice, including medication and other psychotherapies.

## Introduction

The WHO predicts that by 2020 depression will be the second most frequent cause of disability worldwide.^1^ In the UK, the estimated treatment cost of mood disorders was £25 billion in 2006, some 1.5% of gross domestic product (GDP).^2^ Although there are efficacious treatments for depression, only half of these individuals respond to psychological treatment and only 30–40% of individuals treated with antidepressants achieve full remission.^3^ Treatment resistance is a common outcome for individuals with depression,^3^ and those with chronic depression are least likely to respond to current available treatments.^4^
*Treatment-resistant depression* (TRD) is depression that does not respond to adequate intervention, whereas *chronic depression* is depression lasting more than 2 years. In practice, chronic depression and TRD overlap, with many patients meeting both definitions. The term *refractory depression* (RD) encapsulates both definitions.

Research on intervention for RD is sparse, and most have focused on pharmacological or somatic methods. A recent systematic review of trials of medication for TRD reported many conceptual and methodological problems relating to consensus on defining and assessing RD, or on adequate response to treatment.^3^ Another review identified only four trials of psychotherapeutic treatment for TRD, none of which recruited more than 25 participants.^5^ Most such trials also exclude the most severely disturbed individuals, for example, those with comorbid personality disorder (PD) who are known to respond less favourably to existing treatments for acute depression, notably cognitive behavioral therapy.^4^

Few psychotherapy trials focus on patients with RD because current treatments may not be designed to meet their needs. One exception is Cognitive Behavioral Analysis System of Psychotherapy (CBASP) which was developed specifically to respond to chronic depression.^6^ In one trial, depressed individuals who did not respond to nefazodone, an antidepressant and were randomised to receive CBASP had a better response rate than those who continued to receive nefazodone only.^7^ However, a recent large trial showed when an individualised regimen of antidepressants was augmented by either CBASP or brief supportive psychotherapy (BSP) in partial or non-responders, neither psychotherapy added significant benefit to medication; only 38% derived clinically significant improvement from further medication or psychotherapy.^8^ This study reflects earlier findings from the Sequenced Treatment Alternatives to Relieve Depression study (STAR*D) which found that, among patients who failed to respond to antidepressant medication (ADM), fewer than one-third benefited from adding or switching to, cognitive therapy.^9^
^10^ Finally, although the Re-ChORD trial showed that a package of group interpersonal psychotherapy, medication and occupational therapy achieved better remission rates than treatment as usual (TAU) at the end of the treatment trial, it lacked data to show that these gains were maintained.^11^

This protocol outlines a randomised controlled trial of Radically Open Dialectical Behaviour Therapy (RO-DBT), a novel psychotherapeutic treatment for RD.^12^
^13^ RO-DBT arises from neurobiosocial theory^14^ and the observation that current treatments neglect the role of emotional over-control in RD. It proposes that, although the ability to inhibit competing urges, impulses, behaviours and desires is valued by most societies,^15^ too much self-control can be problematic. Excessive self-control has been linked to social isolation, aloof interpersonal functioning, maladaptive perfectionism, disingenuous emotional expression and mental health problems like anorexia nervosa, obsessive-compulsive PD and chronic depression.^16–20^ Of the unipolar depressed patients, 40–60% meet criteria for comorbid PD;^21–23^ over-controlled PDs, notably paranoid, avoidant and obsessive-compulsive, are the most common and least likely to respond to treatment.^4^
^21^
^24^ Children exhibiting behavioural over-controlled traits like shyness, timidity, restrained emotional expression and risk aversion are more likely to develop internalising disorders and become socially isolated adults.^16^
^17^
^25^
^26^ Adults with chronic depression are characterised by over-controlled traits, including greater self-criticism, impaired autonomy, rigid internalised expectations, excessive control of spontaneous emotion and inordinate fears of making mistakes.^23^

The neurobiosocial theory underlying RO-DBT posits that individuals presenting with problems of over-control are biologically predisposed to exhibit heightened threat sensitivity, diminished reward sensitivity, strong tendencies towards constraint and preoccupation with details.^14^ Heightened biotemperamental threat sensitivity predisposes a person to prioritise the *potential for harm* over the *potential for reward* when entering new or unfamiliar situations, thereby activating sympathetic nervous system (SNS) defensive-arousal and fight–flight responses. These perceptual biases are strengthened by family or environmental histories reinforcing avoidance of risk and masking of emotions. Heightened SNS arousal also triggers withdrawal of social safety engagement responses mediated by the parasympathetic nervous system ventral vagal complex (PNS-VVC).^27^ Unfortunately, when the PNS-VVC is withdrawn and SNS-mediated flight–fight responses dominate, neuroregulatory responses linked with prosocial engagement are impaired, facial expressions become frozen and the ability to express oneself flexibly is lost.^27^
^28^ Inhibited or incongruent expressions of emotion are perceived as inauthentic or untrustworthy by others and thus increases social ostracism.^29^
^30^ Since these responses may create or maintain depressive symptoms, RO-DBT uniquely emphasises both *communicative* and *facilitative* functions of emotional expressions in the formation of close social bonds and empathic behaviours via micromimicry and the mirror neuron system.^12^
^13^
^31^ Therapy includes training patients to relax rigid inhibitory self-control efforts, to activate the VVC-mediated social-safety system, to use non-verbal social-signalling skills linked to the mirror neuron system and the establishment of trust to allow vulnerable self-disclosure, to practice self-enquiry to learn from new experiences and critical feedback, and to reduce maladaptive social comparisons related to envy and bitterness.

Earlier versions of RO-DBT showed promise in two trials of patients with refractory depression and comorbid PD.^32^
^33^ The manualised version of RO-DBT^12^ has also been effective in two open trials of adults with anorexia nervosa.^34^
^35^

### Objectives

Our primary aim is to estimate the effectiveness of RO-DBT in treating RD, compared with TAU. We shall also estimate the cost-effectiveness of RO-DBT relative to TAU alone. We also plan to study moderators of treatment effects and mechanisms of therapeutic change. As RO-DBT emphasises the therapist's role as a model of interpersonal skills, we predict that the development and maintenance of a strong therapeutic alliance will mediate reductions in depressive symptoms. Similarly, since the treatment is challenging, we regard adherence as an important potential mediator.

## Methods

### Design and setting

REFRAMED is a multicentre, randomised controlled trial conducted at three National Health Service (NHS) sites in the UK—Dorset, Hampshire and North Wales. These sites routinely offer outpatient psychological treatment. All trial participants receive TAU, but those allocated at random to the experimental arm also receive 7 months of RO-DBT. We also allocate participants at random between non-therapeutic alternatives designed to facilitate mediational analyses. We measure clinical outcomes at four time points—baseline, and 7, 12 and 18 months after randomisation, using assessors blind to participants’ allocated treatment.

### Participants

#### Inclusion criteria

Participants must be 18 years or older, and have a Hamilton-Depression Rating Scale (HAM-D)^36^ score of at least 15, a current diagnosis of major depressive disorder in the Structured Clinical Interview for DSM-IV Axis I (SCID-I),^37^ and *either* TRD defined as two or more previous episodes of depression *or* chronic depression. In their current episode, furthermore, participants must have taken an adequate dose of ADM for at least 6 weeks without relief.

#### Exclusion criteria

We exclude those who meet criteria for dramatic–erratic PD (Cluster B), bipolar depression or psychosis, or have a primary diagnosis of substance dependence or substance abuse disorder. Patients must have an IQ of more than 70 and speak English well enough to participate in the research, including treatment.

### Procedures

Please see figure 1 for a CONSORT diagram of the REFRAMED study participant recruitment, assessment and follow-up timeline.

**Figure 1 BMJOPEN2015008857F1:**
[figure not shown]
CONSORT diagram of REFRAMED study participant recruitment, assessment and follow-up timeline.

### Recruitment

We recruit participants through mental health clinicians, general practitioners (GPs) and advertisements in clinics and community. Clinical study officers within local NHS organisations handle enquiries and screen potential participants for inclusion criteria and the absence of exclusion criteria by telephone, using a standardised checklist. If eligible and willing, participants attend a second assessment interview.

AAQ-II, Acceptance and Action Questionnaire-II;^38^ AD-SUS, Adult Service Use Schedule;^39^ AEQ, Ambivalence over Emotional expression Questionnaire;^40^ BIDR-SF, Balanced Inventory of Desirable Responding-Short Form (Hart CM, Ritchie T, Hepper EG, *et al* The Balanced Inventory of Desirable Responding Short Form: Reliability, validity and factor structure. submitted manuscript 2012);CALPAS, California Psychotherapy Alliance Scales;^41^ CEQ, Credibility/Expectancy Questionnaire;^42^ CSQ-8, Client Satisfaction Questionnaire–8;^43^ DBT-WCCL, Dialectical Behavior Therapy Ways of Coping Checklist;^44^ EAC, Emotional Approach Coping scale;^45^ EQ-5D-3L, European Quality of Life Questionnaire—5 Dimensions;^46^ FMPS, Frost Multidimensional Perfectionism Scale;^47^ HAM-D, Hamilton Rating Scale for Depression;^36^ ICES, Invalidating Childhood Experiences Scale;^48^ IIP-PD-25, Inventory of Interpersonal Problems-Personality Disorders-25 items;^49^ LIFE-RIFT, the Longitudinal Interval Follow-up Evaluation—Range of Impaired Functioning Tool;^50^ MOPS, Measure of Parenting Style;^51^ MSSI, Modified Scale for Suicide Ideation;^52^ NEO-FFI, NEO Five Factor Inventory;^53^ PANAS, Positive and Negative Affect Scale;^54^ PHQ-9, Patient Health Questionnaire-9;^55^ PNS, Personal Need for Structure;^56^ SBQ, Suicidal Behaviors Questionnaire;^57^ SCID-I and SCID-II, Structured Clinical Interviews for DSM-IV;^37^
^58^ SCS, Self-Compassion Scale;^59^ SSQ3, Social Support Questionnaire;^60^ SVS, Schwartz Values Scale;^61^ UPPS, Urgency Premeditation Perseverance Sensation Seeking scale;^62^ WBSI, White Bear Suppression Inventory.^63^

### Randomisation

Once we receive all baseline questionnaires, we allocate each participant between treatments through an adaptive randomisation algorithm administered by Swansea Trials Unit. This maintains the balance across groups of three stratifying variables chosen as potential outcome moderators, but stochastically rather than deterministically to minimise risk of subversion:^64^
Early onset of depression, that is, before 21 years of ageDepression severe at baseline (HAM-D above 25)Personality disorder (meets SCID-II criteria for cluster A or cluster C)

We also use adaptive randomisation to allocate patients between therapists so as to use as many feasible treatment slots at each centre. The allocation sequence was determined dynamically using a database independently administered at the study's Clinical Trials Unit; the database incorporated a study-specific version of a published dynamic randomisation allocation method,^65^ and the resulting allocations were then sent by email to the Trial Manager for further dissemination to study therapists.

#### Mediation and instrumental variables

To understand the mechanisms by which RO-DBT improves outcomes, we shall conduct mediation analyses to estimate the effects of postrandomisation measures on the pathway from randomisation to outcome. Conventional mediation analyses may be biased by unobserved confounding, that is confounding by unobserved variables related to both the mediators and the outcomes.^66^
^67^ Confounding arises because, following randomisation to treatment arm, patients choose the manner in which they adhere to treatment and the level of adherence; if one patient adheres in a certain way and coincidentally suffers worse depression, confounding ensues. To address unobserved confounding, we shall use ‘instrumental variables’ (IVs) which:
Predict the likelihood that a patient will adhere to treatment;Are unrelated to the study outcome; andAre unrelated to the unobserved confounding variables.

If we can find one or more IVs, we can use methods like two-stage least squares to estimate the unconfounded effect of the mediator. The biggest challenge is to find IVs. Some occur naturally; for example, genes can serve as IVs: one variant of the ALDH2 gene makes it unpleasant for individuals to drink alcohol, facilitating unbiased estimates of the effect of alcohol on health from observational data.^68^ Alternatively, researchers make additional random allocations between options that are not therapeutic in their own right, but may influence mediators;^69^ for example, enhancing the therapeutic environment may enhance alliance (the mediator), but have no direct effect on symptoms (the outcome).

REFRAMED has adopted both approaches to facilitate bias-corrected estimates of the effects of two hypothesised mediators: *strength of therapeutic alliance* and *adherence to treatment.* We randomly allocate all RO-DBT participants to one of eight combinations of contextual non-therapeutic features within a 2×2×2 factorial design:
They receive individual RO-DBT in either a *standard therapy room* or an *enhanced therapy room,* which potentially improves both strength of therapeutic alliance and attendance at treatment;After every session they either *have* or *do not have opportunity to provide written feedback* to *their therapist,* which improves strength of therapeutic alliance;^70^ andThey receive compensation potentially for questionnaire completion either *personally* (via their therapists) or *impersonally* (via mail), again potentially increasing attendance at treatment.

While we recognise that these ploys may have limited influence on our adopted mediators,^71^ we include them both for their potential to reduce bias in our estimates, and to encourage the wider adoption and discussion of these methods in psychotherapy research.

### Intervention phase (29 weeks)

#### Treatment as usual

This control intervention permits participants to receive any psychotherapy or prescribed (ADM) with the exception of standard DBT. We monitor type and amount of psychotherapy, and type of ADM and adherence to it. Reporting these data will better describe this generic intervention. In particular, we do not restrict access to appropriate mental healthcare during follow-up.

#### Radically open-dialectical behavior therapy

This experimental intervention comprises 29 weekly individual therapy sessions lasting 50–60 min, and 27 weekly skills training classes lasting 2.5 h, including a 15 min break (table 2). RO-DBT therapists meet weekly for 1.5–2.5 h, and by telephone when needed.^12^
^13^ While RO-DBT participants receive ADM as prescribed, we strongly discourage them from seeking additional psychotherapy during RO-DBT. The RO-DBT treatment developer and study chief investigator ([name]) does not contribute to the treatment.

**Table 2 BMJOPEN2015008857TB2:** RO-DBT treatment goals and target hierarchy for over-controlled disorders

Primary targets and goals DECREASE severe behavioural over-control, emotional loneliness and aloofness/distance INCREASE openness, flexibility, prosocial signalling and vulnerable expression of emotion	

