### Sample size estimation

Based on an average effect sizes close to one from two RO-DBT pilot trials for RD^32^
^33^ and one pilot trial of DBT for TRD,^73^ we judged it feasible and desirable to power REFRAMED to detect a standardised difference of 0.4 between-groups (RO-DBT and TAU)—likely to be considered clinically relevant by the UK National Institute of Health and Care Excellence (NICE).

In the absence of intraclass correlation, a sample of 200 analysable participants from the three centres would yield 80% power when using a significance level of 5% to detect a mean difference of two points on the HAM-D, equivalent to a standardised difference of 0.4. Since we expect to collect analysable data from 83% of participants, we increased our initial target to 240. To increase the power of our mechanistic analyses, we planned to randomise 144 of these to RO-DBT. As participants receiving RO-DBT are clustered by therapist, we increased the target RO-DBT sample size from 144 to 180 to allow for an intracluster correlation coefficient of 0.025 for HAM-D scores, and an average cluster size of 11. Thus we aim to randomise 276 patients—180 to RO-DBT and 96 to TAU (a final allocation ratio of 15:8).

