### Statistical analyses

For our primary measure of depression (HAM-D), we shall analyse by treatment allocated and use a mixed-effects model to estimate the effectiveness of RO-DBT. This will include random effects to account for clustering of outcomes by therapist, and fixed effects to account for treatment allocation, differences between sites and their interaction. In particular, this model does not assume that all therapists are equally effective.^74^ Covariates will include baseline HAM-D score, diagnosis of PD at baseline and age at first onset of depression. Repeated HAM-D measurements enable us to compare RO-DBT and TAU at 7, 12 and 18 months after randomisation. Secondary analyses will test for interaction between treatment allocation and covariates, and estimate the marginal effect of RO-DBT within strata. If data are missing at random (MAR), these models will be unbiased and efficient. We shall, therefore, analyse missing data thoroughly and qualify our conclusions accordingly.

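### RO-DBT is delivered mostly in group skills classes, but the sample size and primary model allow only for clustering by therapist, so standard errors may be too small and power overstated

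*Protocol article*

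**What the plan says.** The section on radically open-dialectical behavior therapy describes two components. The individual one is given as "29 weekly individual therapy sessions lasting 50–60 min". The group one, which every RO-DBT participant also attends, is "27 weekly skills training classes lasting 2.5 h, including a 15 min break".

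Sample size estimation starts from 200 analysable participants and claims "80% power when using a significance level of 5% to detect a mean difference of two points on the HAM-D". The article treats that difference as 0.4 of a standard deviation. Allowing for 83% analysable data, the target became 240, of whom 144 were to receive RO-DBT. The reason given for a further allowance is this: "As participants receiving RO-DBT are clustered by therapist". On that ground the RO-DBT target rises to 180, with an ICC of 0.025 and 11 participants per cluster on average. The final target is 276, as 180 RO-DBT and 96 TAU.

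The Statistical analyses section gives the primary HAM-D model "random effects to account for clustering of outcomes by therapist". Its fixed part has terms for treatment, site and site-by-treatment, plus covariates.

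The article does not mention clustering by skills class. It does not give class size, the number of classes, who leads them, or how class membership relates to a participant's therapist.

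**The concern.** The trial accepts that shared delivery of treatment can correlate outcomes, and adds 36 participants to the RO-DBT arm for that reason. It applies the argument to the therapist only. Members of a skills class share a leader, peers and sessions for 27 weeks, and the class takes up most of the treatment hours, so the same argument could apply there.

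Positive correlation within classes raises the variance of the RO-DBT mean. A model without a class term may then report a standard error that is too small, and a sample size without a class allowance overstates power. Both errors run towards false precision for the treatment comparison. The article fixes the clustering unit in two places, so this is a stated choice and not merely a detail left out.

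**Working it through.** **Contact time** (inputs from the RO-DBT section)
- Individual: 29 × 50–60 min = 24.2–29.0 h.
- Classes: 27 × 2.5 h = 67.5 h, or 27 × 2.25 h = 60.75 h net of breaks.
- Class share net of breaks: 60.75/(60.75 + 29.0) = 68% to 60.75/(60.75 + 24.2) = 72%.
- Class share gross: 67.5/96.5 = 70% to 67.5/91.7 = 74%.

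**Reproducing the plan's figures** (inputs from Sample size estimation)
- A difference of 2 points at a standardised difference of 0.4 implies an SD of 5. A 5% level is taken as two-sided.
- n per arm = 2 × (1.96 + 0.84)² × 25/4 ≈ 98.1, so 99 per arm and 198 in total, against 200 stated.
- 200/0.83 = 241, against 240 stated.
- Design effect = 1 + (11 − 1) × 0.025 = 1.25; 144 × 1.25 = 180; 180 + 96 = 276.
- The therapist allowance alone reproduces 180 exactly, so it contains no hidden allowance for classes.

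**Power as planned**
- Analysable numbers: 180 × 0.83 = 149.4 and 96 × 0.83 = 79.68.
- SE = 5 × √(1.25/149.4 + 1/79.68) = 0.723.
- Power = Φ(2/0.723 − 1.96) = 79.0%, close to the stated 80%.

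**Adding a class component**

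Assumptions not in the article: m = 6–10 per class, and a class ICC of 0 to 0.10 on top of the therapist ICC. Design effect = 1.25 + (m − 1) × class ICC. The last column applies the article's own rule, 144 × design effect + 96.

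| Class ICC | Design effect | SE | Power | Planned SE / true SE | Total N |
|---|---|---|---|---|---|
| 0 | 1.25 | 0.723 | 79.0% | 1.00 | 276 |
| 0.01 | 1.30–1.34 | 0.729–0.733 | 77.8–78.3% | 0.986–0.992 | 284–289 |
| 0.025 | 1.375–1.475 | 0.737–0.749 | 76.2–77.4% | 0.966–0.981 | 294–309 |
| 0.05 | 1.50–1.70 | 0.752–0.773 | 73.4–75.8% | 0.935–0.962 | 312–341 |
| 0.10 | 1.75–2.15 | 0.779–0.821 | 68.3–72.8% | 0.881–0.928 | 348–406 |

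The ratio column assumes that the fitted model absorbs none of the class variance.

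**Simulation of a therapist-only fit**

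Settings: 150 RO-DBT and 80 TAU participants, 15 therapists, classes of 8 crossed with therapist within site, therapist ICC 0.025, no site terms fitted, 2,000 runs per setting.

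| Class ICC | Model SE / true SE | Type I error |
|---|---|---|
| 0 | 1.00 | 5.6% |
| 0.025 | 0.99 | 5.3% |
| 0.05 | 0.95 | 7.0% |
| 0.10 | 0.91 | 7.0% |

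Monte Carlo error on the type I rates is about √(0.05 × 0.95/2000) = 0.5 percentage points. At 0.025 the test is therefore not visibly distorted; at 0.05 and above it is.

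**The case against.** The strongest reply is that share of contact time shows where the hours go, not how outcomes correlate. A reader might infer that the standard errors *are* too small. The article does not support that: it gives no class ICC and no class size, and with a class ICC of zero the plan is right as it stands.

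A reader might also infer that class membership cuts across therapists, so that the therapist effect absorbs none of it. The article does not say so. It says therapist without specifying the individual therapist, and it stratifies the adherence sample of both sessions and classes by therapist and participant, which leaves some alignment possible. If each class belonged wholly to one therapist, the therapist random effect would pick up most of the class variance and the reported standard error would be nearly right, although the sample size would still lack the allowance. One calculation points the other way. With 11 participants per therapist over a recruitment period of about 167 weeks (March 2012 to May 2015) and even intake, a therapist has about 11 × 29/167 ≈ 2 participants in treatment at a time, so a class of 6–10 would have to mix therapists. That is an inference from averages, not a description of how classes were formed.

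Three further points stand. The site and site-by-treatment terms remove whatever is common to all RO-DBT classes at a site. TAU permits any psychotherapy except standard DBT, so the TAU arm may have unquantified clustering of its own. The statistical analysis plan and full protocol are not shown and might add a class term.

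These points limit the size and certainty of the problem. They do not change the fact that the article names the therapist as the only clustering unit in both places.

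**Conclusion.** The concern holds in conditional form. The article makes no allowance for clustering by skills class, although classes supply about 68–74% of RO-DBT contact time. Standard errors may therefore be too small and power overstated, if outcomes correlate within classes beyond what the therapist and site terms absorb.

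At the trial's own therapist ICC of 0.025 the effect is small: standard errors about 1–3% too small, power 76–77% against 79%, and type I error about 5%. It becomes material at a class ICC of about 0.05 or more: standard errors roughly 4–6.5% too small, power 73–76%, and type I error about 7% in the simulation.

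These figures rest on an assumed 6–10 per class and on class variance that adds to therapist variance. The article's own numbers make the upper end plausible: with even intake, 180 × 27/167 ≈ 29 people are in classes at once, about 10 per site. The article does not support a conclusion that the trial is definitely underpowered or that its primary test is definitely anti-conservative.

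**What to change.** - Add a skills-class random effect for the RO-DBT arm only. Make it nested in therapist, crossed with therapist or multiple-membership, according to how classes were actually formed.
- At minimum, specify this model as a sensitivity analysis before the data are analysed.
- Confirm that class membership is recorded for each participant. Table 1 lists sessions attended, but nothing in the article says that class identity is held.
- State the power as conditional on no class-level correlation, or show it over a range of class ICCs with the class size given.

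Recruitment ended in May 2015, so the sample size cannot be changed. Data collection runs to June 2016, so on the article's timeline the analysis still can be. No new participants or outcome data are needed. The cost is a slightly wider interval and a variance component estimated from few classes, which may be imprecise or fall to zero. That is a fair reason to report the therapist-only and class-extended models side by side.
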